## Abstract

**Background:**

Patients with chronic obstructive pulmonary disease (COPD) are often nonadherent with medications and have poor inhaler technique. Community pharmacists can help to improve health-related quality of life and overall outcomes in patients with COPD. We aim to measure the effectiveness of a systematic, pharmacist-driven intervention on patients with diagnosed COPD.

**Methods/design:**

This pragmatic, parallel-group, cluster randomized controlled trial is designed to determine the effectiveness of a multifactorial, pharmacist-led intervention on medication adherence, inhaler technique, health-related quality of life, health care resource utilization including COPD exacerbations, and use of medications. Participating pharmacies in Newfoundland and Labrador (NL), Canada will be randomly assigned to either the intervention or the control group. The intervention group will deliver an enhanced form of care that emphasizes COPD management. The control group will provide usual care and a COPD education pamphlet. Included patients will be aged 40 years or older, have a physician-confirmed diagnosis of COPD, and be able to answer questionnaires in English. The primary outcomes are the between-group difference in the change from baseline to 6 months in medication adherence using the Medication Possession Ratio (MPR) and the Morisky Medication Adherence Scale (MMAS-8). The secondary outcomes are also measured from baseline to 6 months, and include the proportion of patients with a clinically significant change in adherence, the proportion of patients defined as having “good adherence,” the mean MPR between groups, quality of life as measured by the St. George’s Respiratory Questionnaire, medication inhalation technique using a pharmacist-scored checklist, health care resource utilization and antibiotic and orally administered corticosteroid use for COPD exacerbations. Differences between groups will be analyzed at the individual patient level while controlling for clustering effect.

**Discussion:**

A pharmacist-led COPD intervention has the potential to improve patient medication adherence, thus increasing quality of life, possibly decreasing pulmonary exacerbations and reducing utilization of acute health care resources. Methods and results taken from this study could be used to enhance the delivery of COPD care by community pharmacists in a real-world setting. This would serve to enhance COPD population health and quality of life.

**Trial registration:**

International Standard Randomized Controlled Trial Number (ISRCTN) ISRCTN78138190, registered on 3 February 2016.

**Electronic supplementary material:**

The online version of this article (doi:10.1186/s13063-016-1623-7) contains supplementary material, which is available to authorized users.

## Background

### Background and rationale

Chronic obstructive pulmonary disease (COPD) is a respiratory disease characterized by a state of chronic inflammation, usually as a result of environmental toxins, leading to a progressive loss of airway function and systemic comorbidities [1, 2]. COPD is a significant cause of morbidity and mortality and also represents a high economic and social burden [3]. It is listed as the fifth leading cause of death in the world [4], and the fourth leading cause of death in Canada [5]. The overall societal cost of COPD in Canada in 2011, including direct and indirect costs of the disease, was CAN $4.52 billion [6]. Moreover, COPD exacerbations account for more than 50 % of the total health system costs of COPD [2, 7]. The prevalence of COPD is increasing, and although a large proportion of patients remain undiagnosed, they contribute a comparable health care burden to those who have been diagnosed [8].

The approach to COPD management is multifactorial and consists of nonpharmacological as well as pharmacological strategies in order to reduce symptoms, improve quality of life, reduce exacerbations, and slow disease progression [1, 2, 9, 10]. Unfortunately, rates of adherence for medication use in those with COPD are particularly low. The World Health Organization estimates a 50 % adherence rate for patients with COPD [11], while many studies report adherence rates in clinical practice to be between 40 and 60 % [12–17]. There are factors unique to COPD that predispose patients to adherence issues, including the chronic nature of the disease, complex medication regimens, significant comorbidities, and periods of disease stability between exacerbations [16, 18].

Nonadherence has a significant impact on a patient’s outcome, increasing hospitalization and exacerbation rates [10, 19, 20]. Indeed, multiple studies have shown an association between nonadherence in COPD and clinical and economic outcomes [21]. A post-hoc analysis of the Towards a Revolution in COPD (TORCH) trial indicated that patients with more than 80 % adherence had a mortality rate of 11.3 % as compared to 26.4 % in those with adherence of 80 % or below with annual hospitalization rates for exacerbations being 0.15 for adherent patients and 0.27 for nonadherent patients [10]. Furthermore, another study indicated that better adherence was associated with a 20 % reduction in annual hospitalizations [20].

Pharmacists, as readily accessible primary health care professionals with frequent interactions with patients, play a unique role in the health care system. Moreover, community pharmacies can act as cost-effective primary care platforms for improving medication adherence, inhalation technique, and health-related quality of life in COPD [22–25]. A multifactorial, individualized approach to COPD treatment has been suggested by many studies [2, 15, 16, 22–25], with pharmacists playing a major role.

Our multifactorial intervention represents the highest level of care available to COPD patients within the current scope of practice of pharmacists in Newfoundland and Labrador (NL), Canada, and allows us to compare the best possible care to the current level of care provided to COPD patients in the community.

### Objectives

The primary objective of this study is to test the effect of a multifactorial intervention at the community pharmacy level on patient adherence to respiratory medications in patients with COPD. Secondary objectives include assessing the impact of the intervention on quality of life, inhaler technique, and the sustainability and cost-effectiveness of these enhanced services. We hypothesize that the intervention will lead to improved adherence and more effective use of medication such as: better inhalation technique, and being prescribed more appropriate therapy for disease severity.

### Trial design

This trial is a pragmatic, parallel-group, cluster randomized controlled trial (RCT). Pharmacies will be allocated in a 1:1 ratio, and the data analyzed using the individual as the unit of analysis according to a superiority framework. A completed Standard Protocol Items: Recommendations for Interventional Trials (SPIRIT) checklist for the trial is available (see Additional file 1).

## Methods/design

### Study setting

The following study will be implemented in community pharmacies throughout NL. A complete list of study sites as of September 2016 is available in Additional file 2.

### Eligibility criteria

Inclusion restrictions were minimized in order to retain the pragmatic nature of the study design. All community pharmacies in NL holding a valid pharmacy licence will be eligible to participate.

The patient inclusion criteria are as follows:Physician-diagnosed COPDAge 40 years or older at trial enrollmentThe ability to answer questionnaires in English

Patients will not be eligible to participate in the study if they have:Severe disease, defined as a known Forced Expiratory Volume in 1 s (FEV1)/Forced Vital Capacity (FVC) of below 30 %A diagnosis of dementia or a prescription for cholinesterase inhibitorsA terminal illnessPhysician-diagnosed asthmaParticipation in another clinical trialThey do not provide consent

### Interventions

Staff pharmacists working at all participating pharmacies from both arms of the study will be offered training on the design of the study, including how to administer questionnaires, proper patient recruitment, and consenting of patients. The intervention group pharmacists will also receive additional training on how to administer the intervention to a patient as well as an overall “refresher” on COPD management. In the event that additional staff pharmacists at the recruited pharmacies are interested in participating in the study, they will be provided with the required training as needed, (see Additional files 3, 4, and 5 for training materials).

Interested patients will be identified through the use of inhaled medication or a known diagnosis of COPD. Posters and shelf-talkers will also be used to direct interested patients to the pharmacist for screening. The recruiting pharmacist will determine whether or not the patient meets the study criteria. The pharmacist will collect relevant information from the patient directly, or from their physician by telephone or fax in order to complete the Patient Screening Form. Figure 1 provides a flow chart of the consent and data collection process. Data collection and delivery of the intervention may be split into two pharmacy visits of no more than 2 weeks apart.

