### Recruitment

Pharmacists will be recruited primarily via email through the provincial pharmacy associations, with follow-up email and mail requests as needed. Patients presenting with a new prescription or refill for COPD medications will be approached by the pharmacist to gauge their interest in participating in the study.

We will provide ongoing support and work closely with pharmacies to ensure that recruitment targets are appropriate for the community they serve. Moreover, we will aim to monitor the recruitment process through regular communication via site visits, telephone calls, and emails to discuss any issues or challenges that might arise.

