### Randomization

Randomization will be at the level of the community pharmacy. A random number list will be generated using Excel 2013 (Microsoft Corporation) and pharmacies will be assigned to either intervention or control in a 1:1 ratio by the research assistant as they are recruited.

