### Blinding

It will not be possible for participating pharmacies to be blinded to which group they are assigned due to the nature of the intervention. The data analyst will be blinded to treatment assignment.

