## Discussion

This study protocol presents the design of a pragmatic, cluster RCT to determine the effectiveness of a multifactorial pharmacist-driven intervention on medication adherence, inhaler technique, health-related quality of life, health care resource allocation, and use of medications including orally administered steroids and antibiotics during the study period.

COPD management in Canada remains suboptimal, with significant care gaps and patients experiencing poor outcomes and high exacerbation rates [40]. COPD has received considerably less attention in adherence research than asthma, diabetes, cardiovascular disease, and other chronic health conditions [41]. Thus, there is a need for additional evidence with regards to therapy adherence in COPD patients. Several adherence interventions have been studied in RCTs, but few of these have focused on COPD patients. Viswanathan et al, identified 62 RCTs in a systematic review, representing 18 different interventions designed to improve adherence to medications for chronic diseases [42]. However, none of the reviewed studies included COPD or addressed polypharmacy.

Chronic disease management would be assumed to be most successful when care is given through collaboration of health care team members and patients, and includes patient education and monitoring. Viswanathan et al. [42] concluded that the collaborative care approach was particularly effective in improving adherence. This has potential application for the treatment of COPD.

In a literature search of adherence interventions [43], key limitations in many studies addressing adherence revolve around three main points: reliance on inadequate adherence measures; inclusion of a convenient sample of patients; and assessments of intervention outcomes artificially boosted by attrition of least adherent participants. Our study overcomes these limitations; first by depending on pharmacy management software, giving insight into patient adherence; second by appropriate randomization to include a wide range of COPD patients through broad inclusion criteria and a follow-up plan; and third by assessing our primary outcome through both the MPR and the MMAS-8.

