Additional strengths of our study include the pragmatic design of the study which allows the observed process to reflect real-world practice as accurately as possible. Systematic recruitment of participants via community pharmacies will increase the trial’s internal validity. Moreover, our choice of cluster randomization at the level of the pharmacy decreases the potential for contamination of the control as each pharmacist in either the intervention group or the control group will only be providing either usual care or the intervention, not both. Our intervention, though comprehensive, is relatively simple and easily applicable to the clinical setting and addresses both patient behavior and also the pharmacist-patient relationship. We will also measure outcomes beyond adherence alone, including disease-focused and patient-focused outcomes (e.g., health care resource utilization and quality of life).

There are also limitations of this study design. We are measuring our primary outcome indirectly via pharmacy records (MPR) and patient self-report (MMAS-8). Although the MMAS-8 tool has been validated, using direct adherence assessment tools, such as biochemical markers, respiratory device counters or electronic pillboxes, may potentially provide more accurate results. However, utilizing biochemical tests or potentially cumbersome respiratory device counters to measure adherence would be costly and impractical and would require repeat hospital visits and participant inconvenience, which would detract from the pragmatic nature of this study. There is also the potential for patients to interfere with respiratory device counters and thus they may not reliably provide superior measurement of adherence compared to the MPR and the MMAS-8. Another limitation includes potential selection bias due to pharmacists preferentially recruiting patients who they know are at higher risk of medication nonadherence to intervention pharmacies.

There will be no publication restrictions for the full trial results, and publication will be sought in peer-reviewed journals. The authors plan to hold stakeholder meetings to disseminate study results, as well as present the results at local and national conferences.

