### Trial status

Pharmacy recruitment and intervention training began in February 2016 and patient recruitment began in May 2016.

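### Pharmacists who know their arm recruit the patients after allocation; the protocol concedes the selection risk but states no safeguard and claims protection that randomizing pharmacies cannot give

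*Protocol article*

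**What the plan says.** The order of events can be read from five sections of the protocol article.

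- **Randomization:** "pharmacies will be assigned to either intervention or control in a 1:1 ratio by the research assistant as they are recruited".
- **Trial status:** "Pharmacy recruitment and intervention training began in February 2016 and patient recruitment began in May 2016".
- **Blinding:** "It will not be possible for participating pharmacies to be blinded to which group they are assigned due to the nature of the intervention". Only the data analyst is blinded.
- **Interventions:** "The intervention group pharmacists will also receive additional training on how to administer the intervention to a patient", so the training itself reveals the arm. On eligibility, "The recruiting pharmacist will determine whether or not the patient meets the study criteria". Posters and shelf material also steer interested patients to the pharmacist.
- **Recruitment:** "Patients presenting with a new prescription or refill for COPD medications will be approached by the pharmacist to gauge their interest".

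Data collection methods adds that the pharmacists obtain consent. Sample size calculation asks for about seven patients from each of 20 pharmacies.

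The Discussion points both ways. Among the limitations it lists "potential selection bias due to pharmacists preferentially recruiting patients who they know are at higher risk of medication nonadherence to intervention pharmacies". Among the strengths it says that the study overcomes the convenience-sample weakness of earlier adherence trials, "second by appropriate randomization to include a wide range of COPD patients through broad inclusion criteria and a follow-up plan", and that recruiting systematically through community pharmacies raises internal validity.

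Statistical methods plans an unadjusted analysis, with adjustment for baseline covariates, including baseline adherence, as a secondary analysis.

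**The concern.** Randomizing pharmacies makes the pharmacies comparable in expectation. It makes the patients comparable only if entry to the trial does not depend on the arm. Here the person who invites, screens and consents each patient knows the arm, and the article describes no pre-allocation identification of patients, no recruiter unaware of the arm, and no rule that patients be approached consecutively.

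Two kinds of selection follow, and they behave differently:

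- **Selection on past adherence**, which the Discussion itself expects. Patients recruited because their adherence is low tend to improve without any intervention. The primary outcome is the change in MPR, so an intervention arm that starts lower gains from regression to the mean.
- **Selection on traits that are not recorded**, such as motivation or rapport with the pharmacist. These are not among the example covariates in Statistical methods, and adjusting for baseline does not remove their effect.

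Either could lead the trial to credit the intervention with a difference in who was enrolled.

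**Working it through.** **Inputs from Sample size calculation:** SD 30 MPR points, baseline/follow-up correlation r = 0.6, target difference 14 points, ICC 0.05, 7 patients in each of 20 pharmacies (70 patients per arm), type 1 error 5 % (taken as two-sided; the article does not say).

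**Inputs assumed here:** the size of the baseline gap and of any unrecorded shift. The article gives neither, so ranges are shown.

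The plan's 140 patients were checked first. A two-sided change-score calculation gives 150 in total, and a baseline-adjusted one gives 120. The stated figure lies between them. That is a separate matter and does not affect this point.

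**Standard errors**

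- Design effect: 1 + 0.05 × (7 − 1) = 1.3.
- Change score: SD = 30 × √(2 × (1 − 0.6)) = 26.83; SE of the arm difference = 26.83 × √(2 × 1.3 / 70) = 5.17.
- Baseline-adjusted: SD = 30 × √(1 − 0.6²) = 24; SE = 24 × √(2 × 1.3 / 70) = 4.63.

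**Part 1: selection on baseline adherence.** Suppose the intervention arm starts g points lower. With equal SDs at both times, the expected 6-month gap is r × g, so with no true effect the difference in change is (1 − r) × g = 0.4 × g in favour of the intervention.

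| Assumed gap g | Bias in unadjusted change | Share of 14 points | Two-sided rejection rate with no true effect |
|---|---|---|---|
| 5 | +2.0 | 14 % | 6.7 % |
| 10 | +4.0 | 29 % | 12.1 % |
| 14 | +5.6 | 40 % | 19.1 % |

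If the selection acts through the recorded baseline MPR, adjusting for baseline MPR removes this bias. The same gap works the other way when 6-month levels are compared without adjustment, as in the secondary outcome of mean MPR: −0.6 × g, or −3.0 to −8.4 points.

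**Part 2: selection on unrecorded traits.** Suppose such selection shifts 6-month MPR, given baseline, by 2, 5 or 10 points. The baseline-adjusted analysis then rejects a true null in about 7.2 %, 19.1 % or 58.0 % of trials. These figures show sensitivity only. Nothing in the article indicates which shift, if any, would occur, or in which direction.

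**The case against.** Four arguments can be made for the plan.

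1. **The bias is disclosed.** The Discussion names it and gives its direction, so it is not concealed. That stands. What remains is that disclosure is paired with no stated countermeasure and with contrary claims of strength. Pharmacists in both arms are offered training that covers recruitment, but the training materials and the flow chart are not shown. The finding is therefore that no safeguard is stated in the article, not that none exists.
2. **A reader might infer that pharmacists hand-pick patients.** The text does not say so. Recruitment most naturally describes approaching patients as they present. The number of eligible patients per pharmacy is not given, so seven may be scarce rather than a choice from many. Posters bring in some patients whom the pharmacist did not single out. However, nothing stated enforces consecutive approach, and the limitation shows that the authors themselves see a risk of preferential recruitment.
3. **A reader might infer that no analysis can repair the damage.** That goes too far. Adjustment for baseline adherence addresses the one mechanism that the Discussion names. Only unrecorded traits escape it. The weakness is that adjustment is ranked as secondary.
4. **A reader might want one figure for the unrecorded part.** A trait correlated 0.2 to 0.4 with outcome given baseline, with a 0.5 SD imbalance, would give 0.2 to 0.4 × 0.5 × 24 = 2.4 to 4.8 points, or 17 to 34 % of 14. Both inputs are invented, and selection of motivated patients could offset selection of nonadherers. The documents support no estimate.

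It can also be said that the convenience-sample sentence concerns representativeness rather than balance between arms, and that it credits broad criteria as well as randomization. That is fair, but randomizing pharmacies makes a patient sample no less convenient, so the sentence is wrong on that reading too.

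**Conclusion.** The point holds in a limited form. Allocation comes before patient identification, and recruiters who know the arm control approach, eligibility and consent. The protocol concedes the resulting risk, states no safeguard, and makes two claims in the Discussion that conflict with the concession.

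The part that can be sized is regression to the mean in the unadjusted change score: +2.0 to +5.6 points for an assumed baseline gap of 5 to 14 points. This rests on the plan's correlation of 0.6, equal SDs at both times, and selection through the recorded baseline MPR. The gap itself is an assumption. Making baseline adjustment primary would deal with this part. The part due to unrecorded traits would survive adjustment, and neither its size nor its direction can be derived. The documents do not support a claim that the trial is biased by a known amount, or that its net bias favours the intervention.

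**What to change.** 1. **Recruitment rule and log, both arms.** Require pharmacists to approach, consecutively and until the target is reached, every presenting patient aged 40 or older with a COPD medication. Keep a coded log of each patient screened, with the reason for any non-enrolment and the recruitment route, and report it by arm.
2. **Candidate list, pharmacies not yet allocated.** Before allocation is disclosed, generate and date-lock a dispensing list of candidates. Keep it in the pharmacy, so that no patient information leaves before consent, and use it to check who was approached.
3. **Analysis.** Make the analysis of MPR adjusted for baseline MPR the primary one. Add a sensitivity analysis that leaves out self-referred patients.
4. **Text.** Delete the Discussion claims that randomization overcomes convenience sampling and that systematic recruitment increases internal validity.

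The cost is a short log, one dispensing report for each pharmacy still to be allocated, slightly slower recruitment and a protocol amendment. No patients are added. Pharmacies already allocated cannot have a pre-allocation list, and the pharmacist who knows the arm still screens and obtains consent, so some bias will remain. The log will help to show it.
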